##### Preliminary assessment of implementation context

Although this study is an intervention development study, the mixed-methods design will allow us to gather preliminary data in regards to implementation context and information transfer that inform future multisite trials. We will conduct individual qualitative interviews with 4–5 key stakeholders at 6 months following implementation of the CCI. These interviews will gather data regarding perceptions of providers and leadership concerning barriers and facilitators to CCI adoption, tools needed to deliver the intervention consistently, resources needed to maintain the CCI long-term, and adaptations needed to integrate the CCI into regular practice. Qualitative data from exit interviews will be triangulated to examine themes related to barriers and facilitators of CCI adoption, stakeholder and organizational satisfaction with the CCI, and acceptability of the CCI. Additionally, we will measure the following costs associated with CCI implementation: training hours (study staff and provider time) and equipment and other resources costs.

##### Patient outcomes

Patient information will be de-identified for the study, and the research team will not have access to any private health information. Patient outcomes will be extracted through the mobile dashboard and medical chart review. No patients will be contacted for the purposes of this intervention development study; however, we recognize the importance of assessing patient outcomes in future trials. De-identified patient demographic data including age, gender, sexual orientation, race, ethnicity, educational attainment, employment status, HIV status and length of time since diagnosis, viral load, and type of substance use problem will be extracted through the dashboard on all patients entered into the system by providers. Dual care retention data will be extracted through the dashboard in regards to (a) number of appointments attended at the HIV and substance use clinics, (b) number of appointments missed, and (c) number of patients who were not retained in care.

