##### Intervention

The CCI will consist of a mobile application developed for treatment providers, an interagency communication protocol, and a training protocol. The mobile application will be developed on a secure portable platform that providers will access through study-provided tablet devices. The CCI dashboard will be user friendly and easily navigable. The application will feature a secure messaging center for providers to directly communicate. Other application features will include: (a) resources for methods of identifying patients in need of dual care, (b) a system to refer patients to treatment, (c) ability to track patients’ access and utilization of services, (d) real-time patient care notifications, (e) identification of a patient’s care team, and (f) up-to-date lists of resources and evidence-based recommendations for treatment options. The CCI will provide a secure platform that will enable the transfer of patient health information between providers, yet will not be linked in the same electronic health record system, adding an additional level of privacy for patients who do not wish for non-HIV/SUD providers to have access to this sensitive data. These features of the CCI prototype are based on preliminary work [22]; however, the final app will reflect data gathered from the Phases 1 and 2 of the study.

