##### Measures

The framework identified in Fig. 1 has informed the battery of measures. Assessments will focus on organizational-, provider-, and patient-level domains (see Table 3). Primary outcomes will be feasibility and acceptability of the CCI and assessment procedures to be used in a larger trial [35]. Organizational outcomes will include pre- and post-intervention assessments of each clinic to gather data on organizational structure and procedures for care coordination. Provider outcomes will include feedback on the intervention component in Phase 1 and 2 of the trial; satisfaction of care coordination, frequency and quality of interagency communications, and interagency professional relationships; and potential moderators (e.g., stigma, perceived coercion). Patient outcomes will include demographics, viral load, and retention in dual care. Quantitative measures will be collected via web-based surveys from clinic leadership (n = 8) and providers (n = 60) at baseline and 1-, 3-, and 6-months post implementation of the CCI (Phase 3).

**Table 3 Tab3:** Outcome variables and assessment points

Quantitative measures	BL	Post-T	1-, 3- mos	6 mos	Analysis
Provider-level outcomes					
Provider descriptive information					
Provider demographics	X				Descriptive
Training in HIV and SU issues	X		X	X	Descriptive
HIV/SU treatment experience	X		X	X	Descriptive
Knowledge related to SU/HIV	X	X		X	Descriptive
Coercion assessment scale	X		X	X	Exploratory: Moderator
Provider perception inventory	X		X	X	Exploratory: Moderator
Provider acceptability and usability of the CCI and training protocol					
Satisfaction with training		X			Acceptability
CCI program satisfaction				X	Acceptability
Perceived attributes scale	X		X	X	Exploratory: Mediator
Interagency collaboration and communication					
Levels of collaboration scale*	X		X	X	Quant: Hyp 2
Frequency/quantity of communication*	MDE		MDE	MDE	Quant: Hyp 2
Wilder collaboration factors inventory	X			X	Exploratory: Moderator
Relational coordination					
Relational coordination scale*	X		X	X	Quant: Hyp 3
Organizational-level outcomes					
Organizational descriptives	X			X	Descriptive
Organization readiness	X		X	X	Exploratory: Mediator
Implementation climate scale	X		X	X	Exploratory: Mediator
Patient-level outcomes					
Descriptive information					
Demographics	MDE				Descriptive
Viral load	MDE			MDE	Descriptive
Dual care treatment retention	C/MDE			C/MDE	Quant: Hyp1

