*BL* baseline, *I* implementation, *T* training, *MDE* Data extracted through the mobile app dashboard, *CDE* data extracted through clinic medical records, *EXPL* exploratory, *QUANT* quantitative, *HYP* hypothesis

* Primary Outcome Variable

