#### Hypotheses testing

Given the developmental nature of this study, our primary objective is to establish feasibility and acceptability of the CCI and assessment procedures. The following deliverables will result from this study: evidence-based training model adapted to HIV and substance use providers, mobile application tool for providers targeting care coordination, interagency communication protocol, and a training strategy for the CCI. This study will yield necessary data regarding the acceptability and feasibility of the approach to be implemented in a future larger scale multisite trial [35]. We are well aware of the dangers of relying exclusively on small-scale pilot studies to gauge the promise of a novel intervention [43]. Thus, we primarily will be hoping to find a pattern of results that is supportive of the CCI rather than rigorously testing hypotheses to determine a stable effect size. Hypotheses include: (1) Compared to baseline, providers will demonstrate increased dual care treatment retention as measured by data in the EHR; (2) Compared to baseline, HIV providers will report increased frequency and quantity of communication with substance use providers, and substance use providers will report increased frequency and quantity of communication with HIV providers; and (3) Providers will report improvements in relational coordination as measured by increased scores on the Relational Coordination scale between baseline and follow-up assessment. Group means on continuous variables typically begin to stabilize around 15 participants per group. For dichotomous variables, somewhat larger sample size is needed to provide reasonably stable odds ratios for effect size estimates. Therefore, the proposed sample size of 30 participants per group, even after attrition, will allow us to evaluate the potential of the CCI intervention to improve care coordination while remaining within the budgetary parameters for a preliminary trial.

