Tests of the effects of the intervention on the primary outcome variables (identified in Table 1 at BL, 1-, 3-, and 6-months) will be conducted using repeated measures ANOVAS on change scores. We will examine each organization separately and then develop a composite score to examine change across time. We will use repeated measures mixed model analysis of variance (ANOVA) to assess main effects and between-group effects on the primary and secondary dependent variables. We will test for the normality of the distributions, homogeneity of covariance matrices, and sphericity. If violations of the sphericity assumptions are found, we will use the Greenhouse Geyser Epsilon to adjust the probability of F [44]. Omnibus F testing will be followed by univariate tests to examine if primary outcome variables differ by condition (HIV vs SU provider). Analyses will be conducted using SAS Proc GLM, which allows for maximum use of observations across time even when some data are missing. To determine whether there was an effect of group, time, or a group × time interaction on the primary outcome variables specified a priori: (1) collaboration, and (2) frequency of interagency communication, and on the secondary outcome variable specified a priori: (1) interagency relationships as measured by relational coordination, we will conduct 4 repeated measures ANOVAs with 2 levels of condition (HIV provider and SU provider) and 3 levels of time (baseline, 3-mos FU, 6-mos FU). If the null hypothesis is rejected in omnibus testing, we will conduct further univariate tests of hypotheses for between-groups and main effects and calculate effect sizes for the effects observed across time (Eta squared). In addition, for each primary outcome variable at each follow up point, effect sizes and 95% confidence intervals will be computed.

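### The source of dual-care retention (hypothesis 1) is stated inconsistently, and the app dashboard cannot give a baseline comparable with its 6-month data

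*Protocol article*

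**What the plan says.** **Source.** In Hypotheses testing, hypothesis 1 reads that, against baseline, "providers will demonstrate increased dual care treatment retention as measured by data in the EHR". Patient outcomes says "Dual care retention data will be extracted through the dashboard in regards to" attended appointments, missed appointments and the number of patients lost from care. The same section also says more broadly: "Patient outcomes will be extracted through the mobile dashboard and medical chart review". In Table 3 (Measures), the row "Dual care treatment retention" carries the code C/MDE at baseline and at 6 months. It is marked for hypothesis 1 and has no primary-outcome asterisk. The legend reads "Data extracted through the mobile app dashboard, *CDE* data extracted through clinic medical records"; the code C alone is not defined, but presumably means CDE.

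**Patients.** Demographic and clinical descriptors "will be extracted through the dashboard on all patients entered into the system by providers". No section says which patients are to be entered, or when.

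**System.** Training procedures has the app switched on and the tablets handed out after the three didactic sessions, at the start of the 6-month trial. Intervention says the platform carries patient information between providers "yet will not be linked in the same electronic health record system". The Discussion confirms that there is no EHR integration in this study.

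**Analysis.** Hypotheses testing plans four repeated measures ANOVAs with "2 levels of condition (HIV provider and SU provider) and 3 levels of time (baseline, 3-mos FU, 6-mos FU". The outcomes named for them are collaboration, communication frequency and relational coordination. The Abstract, Table 1 and Table 3 all place patient data at baseline and 6 months only.

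**The concern.** A before-after comparison without a control group is only as good as the sameness of the two measurements. Here the text leaves open which system supplies each of them. One permitted combination is a baseline from clinic records on all dual-care patients and a 6-month figure from the dashboard on those who were entered. The two figures would then differ in population, in length of observation and in how attendance is recorded, so they could differ with no effect of the intervention.

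The Discussion acknowledges that there is no control condition, so nothing in the design would expose such an artefact. Retention is the first-listed hypothesis, and Preliminary analyses gives effect-size estimation as a goal. A distorted estimate could therefore carry over into the planned multisite trial.

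**Working it through.** The protocol gives no retention rate, patient count or entry pattern, so there is no stated figure to reproduce. The check sets the statements side by side and then shows how large the artefact could be under declared assumptions.

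**1. Source**

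| Place | Source of retention | Times |
|---|---|---|
| Patient outcomes, retention sentence | Dashboard | not stated |
| Patient outcomes, general sentence | Dashboard and chart review | not stated |
| Hypotheses testing | EHR | compared with baseline |
| Table 3 | C/MDE | baseline, 6 months |

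The app is not integrated with the EHR, so the choice of source changes which patients and appointments count. This is a conflict between statements, not a detail left to a later document.

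**2. Baseline.** The app is enabled after training and baseline is before it. The Phase 2 prototype is tested on fake patient data (Present study). No live dashboard data can therefore exist at baseline, yet Table 3 lists dashboard extraction there: as an option for retention and as the only source for demographics and viral load.

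**3. Fit of the model.** The ANOVA has 3 time levels (baseline, 3 and 6 months). Retention is collected at 2 of them, so 0 of 60 providers would have complete data on it. Imputation cannot supply a time point that is never collected. Three outcomes are named for four ANOVAs; if retention were the unexplained fourth, it would still lack the 3-month level.

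**4. Illustration: staggered entry.** Assume true 6-month retention R, a constant loss rate λ = −ln(R)/6, uniform entry over the 6 months, and status scored at month 6 whatever the entry date. A patient observed for s months is still in care with probability exp(−λs). Averaging over s from 0 to 6 gives

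apparent retention = (1 − R)/(−ln R).

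- R = 0.5: 0.5/0.6931 = 0.721
- R = 0.6: 0.4/0.5108 = 0.783
- R = 0.7: 0.3/0.3567 = 0.841
- R = 0.8: 0.2/0.2231 = 0.896

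Against a baseline followed for a full 6 months, R = 0.6 gives 78.3 − 60 = 18.3 points with no true change. The entry pattern drives this result. If entry is uniform over the first 3 months only, s runs from 3 to 6 and the average is (√R − R)/(−ln R/2) = (0.7746 − 0.6)/0.2554 = 0.684, a gain of 8.4 points. If all patients are entered at launch, the gain is zero.

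**5. Illustration: selective entry.** Let p be true retention at both times and r the ratio of the chance of entry for retained against non-retained patients (both assumed). Retention among entered patients is q = pr/(pr + 1 − p). For p = 0.5:

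- r = 0.5: 0.25/0.75 = 0.333, a fall of 16.7 points
- r = 1: no change
- r = 1.25: 0.625/1.125 = 0.556, a rise of 5.6 points
- r = 1.5: 0.75/1.25 = 0.600, a rise of 10.0 points
- r = 2: 1/1.5 = 0.667, a rise of 16.7 points

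At r = 2, p = 0.4 gives 0.8/1.4 = 0.571 (a rise of 17.1 points) and p = 0.6 gives 1.2/1.6 = 0.750 (a rise of 15.0 points). The sign follows r, which the protocol does not determine.

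**The case against.** Several stronger readings are tempting, and the document does not support them.

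- **That hypothesis 1 rests only on app-entered patients.** Chart review is named, Table 3 appears to allow clinic records at both times, and the hypothesis itself names the EHR. A records-based baseline is available. What stands is that nothing rules out mixing the sources.
- **That retention will be inflated.** No passage says that providers choose freely whom to enter, that they favour engaged patients, or that entry is spread over the trial. The statement about entered patients concerns demographics, viral load and similar descriptors, although dashboard retention can likewise cover only entered patients. The app is also meant to identify and refer patients in need of dual care, which could bring in poorly engaged ones and reverse the sign.
- **That the bias is 18 points.** That value needs every assumption in step 4, together with a fully followed baseline cohort.
- **That retention cannot be analysed.** The three-level ANOVA is not expressly assigned to it. Hypothesis 1 is worded in terms of providers, and a two-time-point analysis of provider or clinic summaries would be possible. Details of that analysis may properly sit in a fuller plan.

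The weight of the point is also limited. The stated primary objective is feasibility and acceptability, retention has no asterisk, and the authors disclaim rigorous hypothesis testing. All of this lowers the severity. None of it removes the conflict over source or the dashboard's lack of a baseline.

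**Conclusion.** The concern holds in a limited form. The protocol contradicts itself on where retention comes from, and the dashboard cannot provide a comparable baseline. A records baseline set against app-entered patients at 6 months could show a change with no true effect. Its size and direction are unknown: the illustrations run from a fall of 16.7 points through zero to a rise of about 18 points, all under assumptions that the documents neither state nor exclude. The three-time-level ANOVA does not fit an outcome collected twice, and that outcome is not among those named for it.

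This should be fixed before any patient data are extracted. It does not threaten the study's primary feasibility and acceptability aims.

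**What to change.** 1. In Patient outcomes, Hypotheses testing and Table 3, name clinic records as the single source of retention in both periods, and remove the dashboard code from the retention row.
2. Define the patient set by the same rule before and after, independently of app entry; for example, every patient recorded with both conditions and in care at the start of each window.
3. Define retention identically over a pre-CCI window and a CCI window of equal length.
4. Analyse it as a two-period comparison, separate from the provider ANOVAs: at patient level with allowance for clustering if de-identified linkage is feasible, otherwise on provider or clinic summaries.
5. Report app-entered patients descriptively only. Report patients newly referred into dual care during the CCI window separately, since a cohort already in care at its start leaves them out.

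**Cost.** Chart review and pre- and post-implementation clinic counts are already planned, but those counts are aggregates, so some further de-identified extraction is needed for the pre-CCI window. Patient-level linkage may prove impractical because the partner organizations use different EHR platforms, which is why step 4 has a fallback. The Discussion's own worry about inaccurate EHR documentation of these diagnoses remains, but one source and one rule in both periods make it less likely to distort the comparison.

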### Data analysis plan

#### Preliminary analyses

Considering this is a pilot study, analyses will have the goal of establishing feasibility and estimation of effect sizes, with modest expectations for rejection of null hypotheses. This is especially true regarding analyses containing higher order effects and multiple predictors. Formal quantitative data analyses will be conducted only on those subjects recruited during Phase 3 of the project. Preliminary analyses will include data cleaning and examination of key demographic and baseline variable differences between the HIV providers and the substance use providers. These analyses will be exploratory in nature and used to describe the providers in each clinic. We will summarize variables at both the organizational and provider unit of analysis. Other preliminary analyses will include examinations of patterns of missing data, research dropout rates, distributional properties of dependent and other measures, and correlations among outcome measures.

#### Hypotheses testing

Given the developmental nature of this study, our primary objective is to establish feasibility and acceptability of the CCI and assessment procedures. The following deliverables will result from this study: evidence-based training model adapted to HIV and substance use providers, mobile application tool for providers targeting care coordination, interagency communication protocol, and a training strategy for the CCI. This study will yield necessary data regarding the acceptability and feasibility of the approach to be implemented in a future larger scale multisite trial [35]. We are well aware of the dangers of relying exclusively on small-scale pilot studies to gauge the promise of a novel intervention [43]. Thus, we primarily will be hoping to find a pattern of results that is supportive of the CCI rather than rigorously testing hypotheses to determine a stable effect size. Hypotheses include: (1) Compared to baseline, providers will demonstrate increased dual care treatment retention as measured by data in the EHR; (2) Compared to baseline, HIV providers will report increased frequency and quantity of communication with substance use providers, and substance use providers will report increased frequency and quantity of communication with HIV providers; and (3) Providers will report improvements in relational coordination as measured by increased scores on the Relational Coordination scale between baseline and follow-up assessment. Group means on continuous variables typically begin to stabilize around 15 participants per group. For dichotomous variables, somewhat larger sample size is needed to provide reasonably stable odds ratios for effect size estimates. Therefore, the proposed sample size of 30 participants per group, even after attrition, will allow us to evaluate the potential of the CCI intervention to improve care coordination while remaining within the budgetary parameters for a preliminary trial.

Tests of the effects of the intervention on the primary outcome variables (identified in Table 1 at BL, 1-, 3-, and 6-months) will be conducted using repeated measures ANOVAS on change scores. We will examine each organization separately and then develop a composite score to examine change across time. We will use repeated measures mixed model analysis of variance (ANOVA) to assess main effects and between-group effects on the primary and secondary dependent variables. We will test for the normality of the distributions, homogeneity of covariance matrices, and sphericity. If violations of the sphericity assumptions are found, we will use the Greenhouse Geyser Epsilon to adjust the probability of F [44]. Omnibus F testing will be followed by univariate tests to examine if primary outcome variables differ by condition (HIV vs SU provider). Analyses will be conducted using SAS Proc GLM, which allows for maximum use of observations across time even when some data are missing. To determine whether there was an effect of group, time, or a group × time interaction on the primary outcome variables specified a priori: (1) collaboration, and (2) frequency of interagency communication, and on the secondary outcome variable specified a priori: (1) interagency relationships as measured by relational coordination, we will conduct 4 repeated measures ANOVAs with 2 levels of condition (HIV provider and SU provider) and 3 levels of time (baseline, 3-mos FU, 6-mos FU). If the null hypothesis is rejected in omnibus testing, we will conduct further univariate tests of hypotheses for between-groups and main effects and calculate effect sizes for the effects observed across time (Eta squared). In addition, for each primary outcome variable at each follow up point, effect sizes and 95% confidence intervals will be computed.

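### The plan gives two incompatible repeated-measures analyses of the intervention effect; under the change-score one, the time test cannot detect an early gain that then holds steady

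*Protocol article*

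**What the plan says.** All of this is in the protocol article, Data analysis plan, under Hypotheses testing, unless another place is named.

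- **Change-score specification.** Tests of intervention effects on the primary outcomes, cited at baseline and months 1, 3 and 6, "will be conducted using repeated measures ANOVAS on change scores".
- **Baseline-as-level specification.** Later in the same paragraph, the tests of group, time and group × time use "2 levels of condition (HIV provider and SU provider) and 3 levels of time (baseline, 3-mos FU, 6-mos FU"). Baseline is now a level, and month 1 is absent.
- **Follow-up tests.** After the omnibus F come "univariate tests to examine if primary outcome variables differ by condition (HIV vs SU provider").
- **Estimates.** The paragraph ends by promising effect sizes and 95% confidence intervals for each primary outcome at each follow-up. These do not depend on the omnibus result. Eta squared and the further univariate tests do.
- **Hypotheses.** Hypothesis 2 is a rise from baseline in communication, stated separately for HIV and for substance use providers. Hypothesis 3 reads "Providers will report improvements in relational coordination as measured by increased scores on the Relational Coordination scale between baseline and follow-up assessment".
- **Visits.** The Abstract, Table 1 and Measures plan provider assessments at baseline, 1, 3 and 6 months. Participants and setting lists a payment for the 1-month follow-up.
- **Design.** The Discussion states that there is no control condition. Participants and setting names one HIV clinic and one SUD treatment organisation.

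**The concern.** The two specifications differ in outcome scale (changes or raw scores), in whether baseline is a time level, and in whether month 1 is included. An analyst could follow either and claim to have followed the protocol, and could choose after seeing the results.

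The choice matters because the study has a single arm. The effect of the intervention can appear only as change from baseline. A time effect computed on changes at the follow-ups asks whether those changes differ from one another. It does not ask whether they differ from zero. Training with a competence check is completed before the application is switched on, so a gain that appears early and then stays level is plausible. That is the pattern this test cannot see.

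**Working it through.** **What the time F tests.** Let μ₀, μ₁, μ₃, μ₆ be the mean scores at baseline and months 1, 3 and 6, and let D_j = Y_j − Y₀ for j = 1, 3, 6. The time effect on D tests

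μ₁ − μ₀ = μ₃ − μ₀ = μ₆ − μ₀, that is, μ₁ = μ₃ = μ₆.

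The baseline mean cancels. For each provider Y₀ is a constant subtracted from every follow-up, so it also drops out of the within-person comparisons. For the profile (0, d, d, d) the null hypothesis is exactly true for every d, and the rejection rate is the significance level.

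**Inputs from the protocol.** 30 providers per group; follow-up above 90% in similar studies (Missing data), taken here as 0.9 × 30 = 27 per group; two provider types; Greenhouse-Geisser adjustment.

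**Assumed, because the protocol gives no value.** Two-sided 5% level; SD 1; equal correlation between visits of 0.3, 0.5 or 0.7; gain d of 0.3, 0.5 or 0.8 SD. The plan states no power figure, so there is none to reproduce.

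**Simulation.** Two-group repeated-measures ANOVA, 2,000 trials per setting. At a true rate of 5% the Monte Carlo standard error is √(0.05 × 0.95 / 2000) ≈ 0.5 percentage points. Rejection rates at correlation 0.5:

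| Profile (baseline, 1, 3, 6 months) | n per group | Time F, changes at 1, 3, 6 | Time F, raw scores at baseline, 3, 6 | Time F, raw scores at all four visits | 95% CI for 6-month change excludes 0 |
|---|---|---|---|---|---|
| 0, 0.3, 0.3, 0.3 | 30 | 4.0% | 65.0% | 64.0% | 61.5% |
| 0, 0.5, 0.5, 0.5 | 30 | 5.0% | 98.4% | 98.6% | 96.9% |
| 0, 0.5, 0.5, 0.5 | 27 | 5.2% | 97.2% | 97.5% | 94.9% |
| 0, 0.2, 0.35, 0.5 (growing) | 30 | 54.0% | 94.5% | 93.2% | 96.2% |
| 0, 0, 0.5, 0.5 (onset at month 3) | 30 | 98.3% | 98.1% | 99.8% | 96.9% |

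Over all 18 sustained-gain settings the change-score time F rejects in 3.9% to 5.4% of trials. The baseline, 3, 6 model rejects in 45% to 100%, and in 89% to 100% for d of 0.5 or more.

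**Is differencing itself the problem?** No. In one simulated data set with baseline kept as a level (change set to 0), the time F was 4.944 on raw scores and 4.944 on changes; the interaction F was 1.913 on both. The differencing is then redundant but harmless. The information is lost when baseline is dropped as a level.

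**The case against.** The best defence is that the fully specified analysis is sound. The group, time and group × time tests are attached to the model that includes baseline, and that model detects an early, sustained gain well. The change-score sentence lists baseline among its time points and does not expressly remove it as a level. The closing promise of effect sizes and 95% CIs at each follow-up would also show the gain if they are taken against baseline. All this stands. A reader might infer that the plan will miss an early, sustained improvement; the documents do not support that.

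Three further inferences also go too far.

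- **That the 1-month data are discarded.** Month 1 is missing from one omnibus time factor, but the per-follow-up estimates cover each follow-up point.
- **That the plan presents HIV versus SU as the intervention effect.** It tests time separately and admits the lack of a control. Comparing provider types is also relevant to Hypothesis 2, which is worded by type.
- **That the change-score test is blind in general.** It is blind to a level profile, much less so to a growing one, and not to onset at month 3.

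The defence does not settle the matter. The sentence introduced as the test of intervention effects is the change-score one. The reference for the effect sizes and CIs is not stated. They are promised for primary outcomes only, while this section calls relational coordination secondary (Table 3 marks it primary). The mean of the change scores, tested against zero, would detect the gain (99.8% at d = 0.5, correlation 0.5, 30 per group), but the plan does not name that test.

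**Conclusion.** Wrong as written, of moderate severity. The paragraph contains two analyses that cannot both be the plan. On the follow-up-only reading of the change-score version, the time test rejects an early, level gain about 5% of the time whatever its size. That result follows from the algebra and needs only the assumed 5% level and a flat profile. The comparison figures (about 97% to 98% for the baseline, 3, 6 model) rest on the assumed d = 0.5 SD and correlation 0.5.

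Severity stops at moderate because the study is a pilot whose primary objective is feasibility and acceptability, with modest expectations of rejecting null hypotheses. Estimating effect sizes is nevertheless a stated goal, so the contrast to be estimated should be fixed in advance.

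**What to change.** In Hypotheses testing:

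1. Delete the reference to change scores and the three-level time factor.
2. State one model on raw scores with baseline, 1, 3 and 6 months as categorical time levels and provider type as the between-subject factor.
3. Name the baseline-to-follow-up contrasts, with 95% CIs, as the intervention estimates. Report them pooled and within each provider type, because Hypothesis 2 is stated by type.
4. Report the same contrasts for relational coordination, whether it is finally labelled primary or secondary.
5. Label HIV-versus-SU comparisons as descriptive, since provider type coincides with organisation.

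The cost is analysis wording only. All four assessments are already scheduled, and no extra data or providers are needed.
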